### Blinding:

Researchers and care givers will be blinded about the allocation of each participant either to the intervention or usual care group. Unblinding will be permissible to care givers at 28 weeks for further entry of data of allocated participant in respective groups.

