### Trial design:

It is a parallel, two-arm (intervention-control) and double blind (care providers and outcome assessors both blind) randomised controlled trial of IV Iron intervention provided to NAID women to replenish their iron stores compared with usual care with prophylactic oral iron. Eligible participants are randomized to the intervention and usual care groups. A 600 sample size will be recruited from three centers. All patients will be followed up till delivery. Post randomisation evaluation will be done at 28 and 36 weeks regarding maternal hemoglobin, serum ferritin, MFI scoring, obstetrical scan for fetal parameters, blood transfusion, development of any complication (preeclampsia, preterm labor, IUGR) and fetal birth weight. Fetal cord hemoglobin and serum ferritin will be checked after delivery. In this way, assessment for primary and secondary outcomes will be done and data set prepared for analysis.

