### Recruitment:

Patient recruitment service providers in outpatient departments will educate the public about the value of clinical trial participation and will encourage the enrollment. All singleton pregnant women with gestational age <20 weeks coming to outdoor department of respective hospitals will be screened for hemoglobin and serum ferritin. If their hemoglobin ≥11g/dl and serum ferritin concentration <30ug/l they will be enrolled for trial after taking informed consent and randomization will be carried out.

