### Methods: Assignment of Interventions

### Allocation:

After recruiting the participants, their data will be entered by investigators sitting in outpatient department in a online computer software program made by technology team that will assign a pin code to every participant which will help in follow up entry of each participant´s data and data analysis by technology team. After randomization, computer software will automatically generate numbers to the participants in an allocation ratio of 1:1 to each group, it will help remove the selection bias. Numbers will be generated from 1-25 randomly by software and after completion of first 25 participants the program will automatically start a new set of 25 numbers. Concealed boxes in sets of 1-25 having IV and oral iron will be made by another team of investigators in respective wards which will be given to the participant having the same computer software generated number.

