### Data Collection and Management:

All pregnant women of gestational age <20 weeks in the participating units will be advised complete blood count. Those having haemoglobin >11g/dl, will have their serum ferritin levels checked. Pregnant women having serum ferritin <30μg/l will be counselled for enrolment into the study and informed consent will be taken after explaining the details of the study. They will be divided into two groups randomly. Therapeutic dose of IV iron will be advised to intervention group and prophylactic dose of oral iron (30-45 mg) will be given to the control group of pregnant women to be continued till delivery. All pregnant women will be followed up till delivery with the usual protocol of monthly visits till 28 weeks then fortnightly visits till 36 weeks and then weekly. Haemoglobin and serum ferritin in both arms will be measured at 28 weeks and 36 weeks of gestation. Development of preeclampsia, preterm birth, blood transfusion, fatigue score, birth weight along with cord blood haemoglobin and serum ferritin will be recorded. Data will be entered into an electronic database (computer software program ASP. NET MVC architecture data collection platform based on SQL 2014 for data normalization) has been purpose designed for the trial with defined multi level user access and separate case report forms for each study visit. The software platform ensures transparent randomisation, allows real-time data acquisition and smooth tracking of the enrolled participants to facilitate standardised, and synchronous data collection across all the study sites, enabling data quality checks and ensuring authenticity of data.

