### Data Monitoring:

Trial steering committee with an independent chair and membership including a patient representative will oversee the study. Data monitoring committee will perform confidential interim analyses, which may be used to determine if an effect is observed and if the study should continue to its planned sample size. Any adverse reaction to IV Iron or blood transfusion will be noted and entered in specific transfusion reaction registers in wards according to hospital protocol. Independent data monitoring committee will systematically review all trial related activities, data entry, will assess compliance with regulatory requirements for clinical trial protocol and clinical quality management plan by principal investigator and all sites support personnels and audit trial quarterly to identify potential risks and help to ensure that compliance issues do not jeopardize the trial.

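### Care-provider blinding is claimed for IV versus oral iron, but the design as described cannot deliver it for staff who infuse or record reactions

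*Protocol article*

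**What the plan says.** Four parts of the protocol article bear on who knows the allocation.

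- **Trial design** describes a "double blind (care providers and outcome assessors both blind) randomised controlled trial of IV Iron intervention".
- **Blinding** repeats the claim more widely: "Researchers and care givers will be blinded about the allocation of each participant either to the intervention or usual care group". It then gives one planned release of allocation: "Unblinding will be permissible to care givers at 28 weeks for further entry of data of allocated participant in respective groups".
- **Allocation and Data Collection and Management** describe the treatments. Supplies are packed as follows: "Concealed boxes in sets of 1-25 having IV and oral iron will be made by another team of investigators in respective wards". Each woman gets the box that carries her number. On the treatments themselves, with the closing words referring to the usual-care arm: "Therapeutic dose of IV iron will be advised to intervention group and prophylactic dose of oral iron (30-45 mg) will be given to the control".
- **Data Monitoring** covers safety recording: "Any adverse reaction to IV Iron or blood transfusion will be noted and entered in specific transfusion reaction registers in wards according to hospital protocol".

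On timing, Recruitment says: "All singleton pregnant women with gestational age <20 weeks coming to outdoor department of respective hospitals will be screened for hemoglobin and serum ferritin". Eligible, consenting women are then randomised. Haemoglobin and ferritin are measured at 28 and 36 weeks, and haemoglobin at 36 weeks is the primary outcome.

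**The concern.** An infusion given in one arm only is visible to whoever gives it, and an entry for a reaction to IV iron states the arm in so many words. Unless a dummy is used or the treating staff are kept apart, care providers are not blind from the moment treatment starts, whatever the label says.

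Two things are at stake. One is the reading of the results. The primary outcome is a laboratory value, which limits the scope for biased measurement. However, care givers also influence some of what is compared, such as whether a transfusion is given (a secondary outcome) and how far routine oral iron is encouraged. A reader told that care providers were blind would discount those routes of bias wrongly. The other is consistency: with three hospitals and no description of who infuses and who records reactions, each site must devise its own arrangement, and these may differ.

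**Working it through.** No figure in the plan decides this point, so the check sets the sections side by side.

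1. **Who is said to be blind.** Trial design: care providers and outcome assessors. Blinding: researchers and care givers. Neither section exempts a team.
2. **What differs between the arms.** IV iron in one, oral iron in the other (abstract, Table I, Data Collection and Management). No dummy infusion or dummy tablet is described. The IV dose is calculated by a formula (abstract, Table I), so some person must work it out and give it for that arm only.
3. **What the boxes achieve.** Numbered boxes hide the next assignment until a woman has her number, which is allocation concealment. They do not hide the treatment once the box is opened and the contents are infused or swallowed.
4. **Who packs the boxes.** Another team of investigators, who must know what each number holds. The article does not say that they infuse, observe women or record reactions, or that they learn which woman has which number.
5. **What a reaction entry reveals.** A ward register entry for a reaction to IV iron identifies the arm to whoever writes or reads it.
6. **When this happens.** No infusion date is given. Screening is before 20 weeks and randomisation follows. If randomisation is prompt, the interval to the planned release at 28 weeks exceeds 28 − 20 = 8 weeks. Trial design treats 28 weeks as a post-randomisation evaluation, and Table I has IV-arm women continue prophylactic iron once stores are replenished. Infusion before 28 weeks is the natural reading, but it is an inference.
7. **What happens after 28 weeks.** Care givers may then be unblinded for data entry. That is 36 − 28 = 8 weeks before the primary outcome, so care-provider blinding is not planned to last to that outcome in any case.

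Steps 1, 2 and 5 do not fit together for any person who both counts as a care provider and gives the infusion or records a reaction. Steps 3 and 4 supply no mechanism that removes the conflict.

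**The case against.** The strongest reply is that nothing here is a strict contradiction. Data Monitoring is written in the passive and names no recorder. If unblinded ward staff, perhaps the team that packs the boxes, gave the infusions and kept the registers, everyone else could remain blind and all the sections could be honoured. This stands as far as it goes. A reader might infer that the unblinding rule and the reaction-recording rule cannot both be followed, and the documents do not support that. They could both be followed with separate staff. What remains is that no such separation is described, while Blinding covers researchers and care givers without exception.

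A reader might also infer that 28 weeks is the sole permitted moment of unblinding and that earlier unblinding for a woman's care is forbidden. The Blinding section does not say so. It describes one planned release for data entry and is silent on the rest. A code-break procedure is detail that an article may leave to the full protocol, and Data Monitoring itself refers reaction handling to hospital protocol. Its absence is not counted here.

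Finally, participants are not claimed to be blind, and a woman who has had an infusion can tell any clinician. This weakens any suggestion that reactions would be handled in ignorance of exposure. It also makes the care-provider blinding harder to sustain.

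**Conclusion.** The point holds as a wrongly stated property of the design. With IV against oral iron, no dummy described and no separate unblinded team described, blinding of care providers is not something this design can deliver for those who give the infusion or record reactions to it. Blinding of laboratory staff, outcome assessors and analysts remains achievable.

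The size cannot be put as a number. The documents give no infusion date, no reaction rate and no basis for estimating bias. The intervals of 8 weeks on either side of the 28-week point are calendar gaps, not measures of harm. It would go too far to infer that reactions will be missed, or that the time before 28 weeks is one of special risk; the article says neither.

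The conclusion rests on two assumptions: that no dummy is used, since none is described, and that IV iron is given soon after randomisation. If the second fails and some infusions fall after 28 weeks, the conflict before 28 weeks shrinks. Blinding would still have been lifted for care givers before the 36-week outcome.

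**What to change.** Reconcile Trial design, Allocation, Blinding and Data Monitoring in three steps.

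- State that the staff who give and observe treatment and record reactions are unblinded, and that they take no part in outcome assessment. Say whether the team that packs the boxes is among them.
- Limit the blinding claim to those who can be blinded: laboratory staff, outcome assessors and analysts. The trial software already has multi-level user access, which could keep the allocation out of these users' view.
- Make the 28-week unblinding rule consistent with the recording of reactions, so that the two sections agree on who knows the allocation and from when.

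The cost is protocol wording and a clear division of roles at each of the three hospitals. If the same people now infuse and assess outcomes, tasks will need to be reassigned. The downside is that the trial can no longer be called double blind with respect to care providers.

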**Methods and Analysis::**

FAIR will be a multicenter randomized controlled trial that will be conducted in multiple clinical academic obstetrics units in Lahore (including Services Institute of Medical Sciences, Lahore, Allama Iqbal Medical College, Lahore and Fatima Jinnah Medical University). Pregnant women at gestational age <20 weeks with hemoglobin 11-13 g/L and ferritin below the threshold (<30 ng/ml) will be invited to take part in the study. Randomization will be done by computer based generated random numbers. One group (usual care or oral group) will be offered routine care prophylactic dose of oral iron (30-45 mg/day) and the other group (intervention arm or IV group) will be offered therapeutic dose of IV iron (dose calculated by Ganzoni formula) in addition to usual care. All patients will be followed up till delivery. Primary maternal outcome will be hemoglobin at 36 weeks’ gestation. Secondary outcomes are fetal birthweight or small for gestational age, preterm birth, preeclampsia, multidimensional fatigue inventory, breast feeding initiation, blood transfusion, and fetal cord ferritin and hemoglobin.

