### Eligibility Criteria:

Selection criteria is established using the PICO or population, intervention, comparison and outcome framework explained in Table-I.

**Table-I T1:** PICO for study population.

	Population	Intervention	Comparison	Outcome
Inclusion	Singleton pregnancy Haemoglobin 11-13 g/L at booking with ferritin below the threshold (<30) Age >18 years of age at recruitment to the study Able to provide written informed consent Patients willing to enroll in study	NAID patients will be divided into two groups by randomization. One group (usual care/oral group) will be offered the routine care prophylactic dose of oral iron which is 30-45 mg and other group (interventional /IV group) will be offered intravenous therapeutic dose of iron to replenish iron stores which is 1000mg calculated by Ganzoni’s formula. They will continue the prophylactic dose after replenishing iron stores. Adherence to intervention protocols will be monitored by proper documentation and laboratory test	Usual care vs intervention arm will be compared for outcome	Primary: Maternal: Hemoglobin at 36 weeks’ gestation to birth Secondary: Neonatal birthweight or small for gestational age, preterm birth, blood transfusion, preeclampsia, multidimensional fatigue inventory, breast feeding avoidance/initiation, neonatal cord ferritin and haemoglobin

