### Data Analysis:

All the statistical analysis will be done on statistical package for social sciences (SPSS). Mean and standard deviation will be calculated for continuous variables like age, gestational age, haemoglobin, serum ferritin levels etc. Frequency and percentages will be calculated for categorical variables like gender. If data are not normally distributed then median will be used. Confounders like age, duration of disease and co morbidities will be controlled through multivariable analysis documented through a statistical analysis plan prepared before the outcome data per group are unblinded. Comparison of outcome will be tested by chi-square and student’s t-test. P value of <0.05 will be significant.

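### Care providers are declared blind, yet the protocol permits unblinding them at 28 weeks for data entry, eight weeks before the primary haemoglobin

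*Protocol article*

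**What the plan says.** The Trial design section describes a "double blind (care providers and outcome assessors both blind) randomised controlled trial". Two parties make up that definition, and care providers are one of them. Participants are not claimed to be blind.

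The Blinding section opens in agreement: "Researchers and care givers will be blinded about the allocation of each participant either to the intervention or usual care group". Its next sentence reads: "Unblinding will be permissible to care givers at 28 weeks for further entry of data of allocated participant in respective groups". This is a general permission tied to a scheduled visit and to data entry. It is not an emergency provision for one woman.

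The Abstract states: "Primary maternal outcome will be hemoglobin at 36 weeks’ gestation". Table-I gives the timing as "Hemoglobin at 36 weeks’ gestation to birth". Under either wording the primary outcome falls at or after 36 weeks.

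Under Data Collection and Management, haemoglobin and ferritin are measured at 28 and at 36 weeks in both arms, with visits every two weeks in between. The same section describes a purpose-built database with several levels of user access and a separate form for each visit. The Allocation section says that the software "will assign a pin code to every participant which will help in follow up entry".

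**The concern.** Two sections of one document give different answers to whether care providers are masked when the primary outcome is measured. A reader of the Trial design section would take them to be masked throughout. A reader of the Blinding section learns that this may stop at 28 weeks.

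The timing is what matters. Haemoglobin is a laboratory value, so biased measurement is not the main worry. It does respond to treatment, and care givers see these women repeatedly between 28 and 36 weeks. A care giver who knows both the 28-week results and the arm may handle the same result differently in the two groups, through further iron or transfusion. The 36-week difference would then mix the effect of the allocated treatment with the effect of knowing the allocation. Transfusion is itself a secondary outcome and a clinician's decision, so it is exposed as well. The delivery outcomes also come after the permitted unblinding.

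**Working it through.** **1. Timing.** Permitted unblinding is at 28 weeks (Blinding) and the primary outcome at 36 weeks (Abstract, Sample Size). The gap is 36 − 28 = 8 weeks, or more under Table-I's wording. With visits every two weeks, 8 / 2 = 4 intervals, hence three visits (30, 32 and 34 weeks) between the two measurements if the schedule is kept.

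**2. Sections side by side.**

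| Party | Trial design | Blinding, before 28 weeks | Blinding, from 28 weeks |
|---|---|---|---|
| Care providers / care givers | blind | blind | may be unblinded |
| Outcome assessors | blind | not named | not named |
| Researchers | not named | blind | no unblinding stated |
| Participants | not claimed blind | not claimed blind | not claimed blind |

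The contradiction is confined to the first row, from 28 weeks on.

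**3. The stated reason.** The reason given is data entry. The Allocation section already provides a PIN for that purpose, and the database has graded access. The follow-up items listed (haemoglobin, ferritin, fatigue score, scan, transfusion, complications, birth weight, cord blood) can be recorded without knowing the arm.

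**4. The plan's own sample size.** Inputs from Sample Size: difference 0.3 SD, alpha 0.05 (taken as two-sided, which reproduces the figure; one-sided gives 191), power 90%, loss 20%.

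- n per group = 2(1.960 + 1.282)² / 0.3² = 234. The t-based version gives 234.5, rounded up to the stated 235.
- With 20% loss: 235 / 0.8 = 293.75, so 294, against the stated 300.

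The sample size reproduces and is not in dispute.

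**5. Illustration of sensitivity.** Let b be the net shift in the 36-week group difference caused by arm-driven co-treatment, in SD units. The documents give no value, so b is an assumption, shown over a range. With 235 per group the standard error of the difference is √(2/235) = 0.0922 SD.

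- Power when the true effect is 0.3 SD and extra treatment of the oral group narrows it: Φ((0.3 − b)/0.0922 − 1.96).
- Two-sided error when there is no true effect: Φ(b/0.0922 − 1.96) + Φ(−b/0.0922 − 1.96).

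| Assumed b (SD) | Power, true effect 0.3 SD | Error rate, no true effect |
|---|---|---|
| 0 | 90.2% | 5.0% |
| 0.05 | 77.3% | 8.4% |
| 0.10 | 58.2% | 19.2% |
| 0.15 | 36.9% | 36.9% |

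The table shows only how little shift a trial designed for 0.3 SD can absorb. It does not estimate what will happen.

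**The case against.** The strongest reply is that the clause permits unblinding without requiring it, names care givers only, and concerns a trial whose primary outcome comes from a laboratory. Care givers may also see the 28-week results whatever the blinding, so a low value could prompt extra iron in either arm. That is fair. Treatment prompted by the result alone is not a blinding failure; what the clause adds is the chance of acting differently on the same result because the arm is known. The documents do not show that this would occur or how large it would be. It is also an inference, though a reasonable one, that the PIN makes the arm unnecessary: the Allocation section does not say that every form can be completed without it.

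Some stronger readings are tempting but not supported:

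- **That the clause cancels double blinding altogether.** Outcome assessors are the other half of the definition, and nothing says that they are unblinded. It would matter if care givers also recorded outcomes, but the article does not say so.
- **That it breaches the Data Analysis section**, which calls for a "statistical analysis plan prepared before the outcome data per group are unblinded". Telling a care giver one woman's arm does not release outcomes by group to those writing the plan. Both provisions can be met.
- **That it causes bias in the fatigue score.** Participants are never said to be blind, so expectation effects on that score would exist without the clause and would survive its deletion.
- **That masking before 28 weeks already fails because no dummy is described.** This argues from silence in a condensed article, which does mention concealed boxes prepared by a separate team.

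**Conclusion.** The contradiction is real and needs no outside fact: the Trial design section has care providers blind without limit of time, and the Blinding section allows that to end eight weeks before the primary outcome. It is a stated rule that conflicts with the stated design, so a separate analysis plan would not resolve it. From 28 weeks the care-provider half of the blinding is not assured, while the assessor half is untouched by the text.

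The consequence is a plausible route to differential co-treatment before the 36-week haemoglobin, in either direction. Its size is unknown. The conclusion rests on two assumptions: that some care givers would use the permission, and that knowing the arm could alter their decisions. The power and error figures depend on assumed shifts and carry no weight as predictions.

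**What to change.** Delete the sentence permitting unblinding at 28 weeks for data entry. Enter the 28-week, 36-week and delivery forms by PIN, with the arm field hidden from care givers through the existing user-access levels until database lock, individual emergency unblinding excepted. If a form carries a field that reveals the arm, such as documentation of adherence to the allocated product, keep that field on a separate form with restricted access.

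If care givers cannot in practice be kept masked, reconcile the Trial design and Blinding sections the other way: drop the care-provider part of the double-blind label and state who is masked, and until when.

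The cost is one sentence, a database permission setting and, under the second option, a less favourable description of the blinding. The documents do not show whether the sites have separate people for giving treatment and recording outcomes, so the sponsor should check staffing before choosing.
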